##### Primary outcome

HbA1c at 12 months post-randomisation will be analysed using a mixed-effects regression analysis, with HbA1c values at six and 12 months follow-up as the dependent variables. Baseline HbA1c values, randomised treatment group, time, and a treatment group-by-time interaction, as well as other important baseline covariates will be included as fixed effects, and the DIAMONDS Coach who delivered the intervention will be included as a random effect, nested within treatment group.

##### Sensitivity analyses

The amount of missing data will be reported for each randomised group, and we will also compare the baseline characteristics of participants who are included in the primary analysis to ensure that any missing data have not produced any imbalance in the groups in important covariates. The amount of missing data will be mitigated by including all data in the primary analysis model, which allows the inclusion of any patient with complete baseline data and valid outcome data at one or more follow-up points. Complier Average Causal Effect (CACE)^47^ analyses will be performed for the primary outcome to assess the impact of compliance with the intervention on treatment estimates.

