### Primary outcome

The primary outcome is the adjusted difference in glycated haemoglobin (HbA1c) between the groups at 12 months postrandomisation. To avoid the inadvertent introduction of differences in measurements of HbA1c through the use of several local laboratories, one central United Kingdom Accreditation Service registered laboratory will be used for all blood sample analyses. Blood samples will be sent to the laboratory from the participating sites. The laboratory will return test results (recorded as mmol/mol and %) to the study team at the University of York (UoY).

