### Assignment of groups

Eligible and consenting participants will be randomised on a 1:1 basis to the DIAMONDS intervention or usual care using computer-generated permuted blocks of randomly varying size. York Trials Unit (YTU) will provide a central web-based randomisation service for R&D teams at sites to use when assigning participant allocations. Participants will then be informed of their allocation during their baseline visit or shortly following.

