#### Statistical analysis

Full analyses will be detailed in a statistical analysis plan (SAP), which will be finalised and made available before the end of data collection. Statistical analyses will be on an intention to treat basis and statistical significance will be at the 5% level (unless otherwise stated in the SAP). Analyses will be conducted in the latest available version of Stata or similar statistical software. Baseline characteristics will be reported descriptively by treatment group. Continuous data will be summarised as means, SD, medians and ranges and categorical data will be summarised as frequencies and percentages. Data will be visually inspected and any imbalance reported. No interim analyses will be conducted.

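### The primary model takes only participants with complete baseline data, so an observed 12-month HbA1c is discarded whenever a baseline value in the model is missing

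*Protocol article*

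**What the plan says.** All references are to the protocol article.

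- **Statistical analysis:** "Statistical analyses will be on an intention to treat basis", with a bracketed proviso that the SAP may state otherwise.
- **Primary outcome (under Statistical analysis):** a mixed-effects regression "with HbA1c values at six and 12 months follow-up as the dependent variables". The fixed effects are "Baseline HbA1c values, randomised treatment group, time, and a treatment group-by-time interaction, as well as other important baseline covariates". Baseline HbA1c is thus a covariate, and the other covariates are not listed.
- **Sensitivity analyses:** the remedy for missing outcomes is the model itself: "The amount of missing data will be mitigated by including all data in the primary analysis model". The rest of that sentence sets the condition for entering the analysis, because the approach is described as one "which allows the inclusion of any patient with complete baseline data and valid outcome data at one or more follow-up points". The section also promises the amount of missing data by group, a check of baseline characteristics among those analysed, and a CACE analysis. It gives no method for a missing baseline value.
- **Primary outcome (under Aim and objectives):** HbA1c is measured at one central laboratory. "Blood samples will be sent to the laboratory from the participating sites", and results come back to the study team afterwards.
- **Assignment of groups:** "Participants will then be informed of their allocation during their baseline visit or shortly following".
- **Eligibility criteria:** type 2 diabetes must be confirmed by a clinician or the medical record. A baseline HbA1c result is not among the criteria.

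**The concern.** The inclusion condition has two parts. The second, at least one follow-up value, is what a repeated-measures model is good for: one missed visit does not remove a participant. The first, complete baseline data, works the other way. It removes people whose primary outcome is known because a covariate is not. In a randomised trial, missing baseline values need not cost any participant.

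Such gaps are plausible here. Blood may be drawn at home and goes to a central laboratory, so a sample lost or unusable there could come to light after the participant has been randomised. The unlisted covariates add further ways to be incomplete.

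Observed primary outcomes are at stake in a trial whose target has been cut from 450 to 380. The named safeguards do not restore them: the baseline comparison describes who was analysed, and CACE concerns compliance.

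**Working it through.** **1. What the rule does.** Take a randomised participant with a valid 12-month HbA1c and no baseline HbA1c. The follow-up condition is met and the baseline condition is not. Baseline is a regressor and not an outcome, so the model cannot use the record unless the gap is filled, and the article names no way to fill it. The participant is dropped, although the sentence says that all data are included.

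**2. Inputs** (Sample size section): difference 5.5 mmol/mol; 5% significance, taken as two-sided; N = 450 for about 90% power; attrition 20%; cluster size 10–12 per Coach with ICC 0.02 in the intervention group; revised N = 380 with baseline to 12-month correlation 0.3 and 88% power. The SD is not stated. Solving for it from 450 and 90% gives about 15.3–15.4 mmol/mol, or 14.6–14.8 if the design effect is applied to both arms. It is carried over because the other assumptions are said to be unchanged.

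**3. Reproducing the stated 88%.** Power = Φ(d/SE − 1.96).
- At N = 450 and 90% power, d/SE = 1.960 + 1.282 = 3.242.
- Moving to N = 380 with residual variance 1 − 0.3² = 0.91 multiplies this by √((380/450)/0.91) = 0.9633, giving 3.123.
- Power = Φ(3.123 − 1.960) = Φ(1.163) = 87.8%, against the stated 88%.

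The SD, the attrition and the design effect cancel, so the result is the same for 10, 11 or 12 participants per Coach. This shows that the two stated pairs of figures agree with each other. It does not verify the SD.

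**4. Dropping a share p of outcome providers.** The base is 380 × 0.80 = 304 analysed. Power = Φ(3.123 × √(1 − p) − 1.960).

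**5. Keeping them instead.** As an approximation, a participant without a baseline value contributes with variance 1.00 instead of 0.91. Total information is then multiplied by (1 − p) + 0.91p = 1 − 0.09p, and power = Φ(3.123 × √(1 − 0.09p) − 1.960).

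| p (assumed) | Analysed if dropped | Power if dropped | Power if kept |
|---|---|---|---|
| 0% | 304 | 87.8% | 87.8% |
| 1% | 301 | 87.4% | – |
| 2% | 298 | 87.1% | 87.7% |
| 5% | 289 | 86.1% | 87.6% |
| 10% | 274 | 84.2% | 87.5% |

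**6. How p could build up.** If each of five covariates were missing independently in 2% of participants, 1 − 0.98⁵ = 9.6% would have incomplete baseline data. Both the number of covariates and the rate are illustrative.

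**The case against.** The strongest reply is that the sentence describes what a mixed model can accommodate and is not an exclusion rule. Full analyses are deferred to an SAP that is not shown. If the SAP imputes baseline values, the baseline data are complete and the sentence is satisfied. Part of this stands: the SAP can settle the matter without contradicting the article. But the article does state the condition for entry and names no imputation, so as written the participants are lost.

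Four stronger readings are tempting, and the article does not support them.

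- **A breach of intention to treat.** The article does not define the intention-to-treat set as everyone with an observed outcome. Nobody is moved between arms or removed for non-compliance, and follow-up continues after withdrawal from the intervention. The remedy below also omits participants with no follow-up HbA1c. The set is less complete than it could be, and no more than that can be said.
- **Bias between arms.** Baseline missingness that arises before allocation is known should not depend on arm.
- **Every baseline failure surfaces only after randomisation.** A refusal is known at the visit. The Assignment of groups section says only when participants learn their allocation, not whether blood is drawn first or whether randomisation waits for it. The pathway figure and the data-collection appendix, which may give the order, are not shown. For samples lost or unusable at the laboratory, late discovery is a reasonable inference but still an inference.
- **A large loss of power.** No rate of missing baseline data is given. The text does not say what the 20% attrition covers, and people without baseline blood may overlap with those without follow-up blood.

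**Conclusion.** The point holds as a matter of efficiency and completeness. The stated condition discards observed primary outcomes for want of a covariate which, at the assumed correlation of 0.3, explains 0.3² = 9% of the outcome variance. That is a poor exchange, and it does not match the description of the model as using all data.

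The size depends on an unknown rate. At 1–2% missing, the loss is under one percentage point of power. At 5% it is about 1.7 points and at 10% about 3.6, nearly all of it recoverable (to 87.6% and 87.5%). These figures assume a two-sided test, a normal approximation at 12 months, an SD implied by the plan's own figures, and a loss that comes on top of the 20% attrition. The finding is one of lost precision only. It deserves correction because the remedy is standard and cheap.

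**What to change.** State in the SAP, and in the protocol at its next amendment, that every randomised participant with at least one follow-up HbA1c enters the primary model. Name one of two methods in advance:

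1. Model baseline HbA1c as an outcome alongside the 6- and 12-month values, with a common baseline mean across arms, and use mean imputation ignoring arm for any other missing baseline covariate.
2. Keep the model as described and use mean imputation, ignoring arm, for all missing baseline covariates, including HbA1c.

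Report the complete-baseline analysis as a sensitivity analysis. Use only observed baseline HbA1c in the subgroup analysis by baseline HbA1c, because imputed values do not suit it.

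The cost is a paragraph of SAP text and a little more analysis work; no new data are needed. There is one small downside. Both methods assume that baseline missingness does not depend on allocation. Any baseline sample taken after allocation was known, for example a repeat of a failed one, should therefore be flagged in the data.

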##### Subgroup analyses

A subgroup analysis will be performed to explore any differential treatment effects for different levels of HbA1c at baseline.^48^ We will also conduct exploratory subgroup analysis by ethnicity and by insulin use status. The results of any subgroup analysis will be treated cautiously, detailed in advance in the SAP and include hypothesised direction of effect, in line with best practice.^49^

##### Secondary outcomes

Secondary outcomes relating to participants’ physical health, mental health and diabetes measures will be analysed using mixed-effects regression analysis for continuous outcomes and logistic mixed models for categorical outcomes. Models will include assessments at all available time-points and will provide an overall treatment effect over 12 months, as well as estimates at individual time-points (six and 12 months), reported as estimates and 95% CIs. Accelerometer data will be collected at baseline and six months post-randomisation. Data will be analysed using the R-package GGIR,^50^ which performs signal processing of the raw data, including auto-calibration, detection of abnormal values, detection of non-wear and calculation of the average magnitude of dynamic acceleration (Euclidean norm minus one g (ENMO)). Descriptive statistics for accelerometer data will be reported for each treatment group at each time point (baseline and six months) and differences between treatment groups will be reported, adjusted for baseline.

### Process evaluation

The process evaluation will draw on a mixed-methods approach, harnessing data from both qualitative and quantitative sources to address questions about whether the intervention was delivered as intended (ie, fidelity) and how outcomes were produced (ie, MoAs). Additionally, the process evaluation will aim to identify contextual and service-level barriers and enablers to post-trial implementation and scale-up, including whether the intervention can support self-management of other LTCs in people with SMI. Drawing on best practice methodology for process evaluations,^51^ we will identify and assess key dimensions related to what intervention activity and content was delivered and how.

#### Intervention fidelity observations

In accordance with the guidance set out by Bellg (2004),^52^ the Intervention Fidelity (IF) framework for the DIAMONDS RCT will measure: (1) adherence (whether the content of the intervention sessions was delivered as it was designed); (2) quality of delivery of intervention sessions (use of Behaviour Change Techniques and the manner/behaviour in which the Coach delivers the programme); (3) duration (mean, SD and range) of intervention sessions and (4) dose (number of sessions delivered). This IF framework was determined and refined through discussions with the research team at the Leicester Diabetes Centre (LDC) and University of Leicester (UoL), the study team and findings from the feasibility study. IF will be achieved by training observers to observe the sessions. For each observation, the trained observers will complete a checklist supported by an IF coding manual which will be developed by the LDC/UoL team. The development process will include drafting the checklist and IF coding manual, testing them by carrying out inter-rater reliability and refining them until the level of agreement is reached.

#### Quantitative approach: data collection and analysis

Quantitative data will be extracted from Coach session logs, the Change One Thing app content management system, and the IF assessments to descriptively summarise:

Number of sessions delivered: mean, SD; session length.Date of sessions (to derive session frequency).Mode of delivery (videocall, phone, in person): frequencies/percentages.List of intervention content areas with number (%) of participants who discussed each content areaAverage duration a participant stayed with the same action plan/content areaAverage number of intervention content areas covered during the total intervention period and in both the workbook and/or Change One Thing app.

#### Qualitative evaluation: recruitment, data collection and analysis

The research team at UoY will conduct semi-structured interviews/focus groups with participants, carers and DIAMONDS Coaches to determine engagement and satisfaction with the intervention. Interviews/focus groups will last approximately 45 min. The recruitment, data collection, and analysis for each of these cohorts are outlined below.

##### Participants

A sample of participants (20–25) will be approached by the research staff at the trusts on completion of the intervention and asked to provide written or verbal consent to take part in these 1–1 interviews. We aim to invite participants with a range of ages, genders, baseline health outcomes, comorbidities, levels of engagement with the workbook/app and levels of intervention completeness to inform sampling. These interviews/focus groups will explore participants’ experiences of intervention delivery and receipt, and any behavioural changes made to support their physical health and well-being.

##### Carers

The research staff at the trusts will be asked to identify, contact and recruit 20–25 carers for participation in the interviews. They will obtain either written or verbal consent. Only carers of service-users participating in the DIAMONDS RCT will be eligible. Once carers have given consent to the research team at the study site and permissions are in place to share contact details, this information will be passed on to the study team at UoY who will be responsible for arranging and conducting the interviews. Similar to the participant interviews, these will last approximately 45 min. For the purpose of this study, carers are defined as unpaid carers who are not subject to working regulations and provide support to a dependent person who they have a social relationship with, such as a spouse, other relative, neighbour, friend or other non-kin.

##### Coaches

On completion of their intervention sessions, all Coaches will be invited to take part in interviews/focus groups. Coach interviews are expected to last 30 min and will explore questions around the DIAMONDS Coach training, delivering the intervention, engagement with Coach support and barriers and enablers to implementing the intervention in existing health and care services.

All interviews/focus groups will be digitally recorded (with participant consent), anonymised and transcribed, with the transcripts forming the data for analysis. An initial thematic analysis^53^ will be conducted using a framework method.^54^ An initial coding framework will be developed, and transcripts checked against the framework to ensure that there are no significant omissions. Codes will be examined across individual transcripts as well as across the entire data set and allocated to the framework. Using aspects of the constant comparison method of analysis, broader categories using linking codes will be developed across the transcripts.

Further analysis will be guided by the MoA framework that extends the Theoretical Domains Framework (TDF).^55^ The TDF offers a robust theoretical basis for understanding implementation problems^56^ and has previously been used to frame the focus of a process evaluation of a behaviour change intervention.^57 58^

### Integrated analysis

A triangulation protocol will be used to explore opportunities to further integrate the quantitative and qualitative data. The sources of data will include IF assessments about adherence and quality of intervention delivery; patient participant and informal caregiver interview data about experiences of intervention receipt and Coach interviews/focus group data about experiences of intervention delivery. Key findings will be compared (in pairs) across the data sets using a convergence coding matrix. For each qualitative theme, we will investigate whether we can identify analogues in the quantitative data. We will then categorise the relationship between findings from the qualitative and quantitative data according to four categories: agreement (convergence in the data), partial agreement (complementary findings but limited overlap), silence (no overlap between quantitative and qualitative data) and dissonance (disagreement between data sets).

### Economic evaluation

The health economic analysis will take the form of a within-trial cost-utility analysis using an NHS and personal social services perspective as recommended by NICE guidance^59^ undertaken over a 12 month period. Additional details of the economic evaluation can be found in online supplemental appendix 7.

### Adverse event reporting, harms and participant withdrawals

#### Adverse events

An adverse event (AE) is any unexpected effect or untoward clinical event affecting the participant (ie, any unfavourable and unintended sign, symptom or disease). It can be directly related, possibly related or completely unrelated to the intervention. Any AEs or serious adverse events (SAEs) will be recorded by the R&D team at sites using specific AE/SAE forms. The reporting period will be from study entry to the last follow-up visit, and all events related to the DIAMONDS intervention will be recorded.

All SAEs are to be reported to the Chief Investigator and will be reviewed by a clinician independent of the DIAMONDS study team. All SAEs will be reported to the Sponsor and Research Ethics Committee (REC) in line with their guidelines. Ongoing review of AEs will take place during the Programme Management Team and PSC meetings.

#### Suicide and self-harm risk management

We have developed a suicide risk protocol for the monitoring of suicide and self-harm risk during all encounters with study participants. Where any risk to participants, due to expressed thoughts of self-harm or suicide is encountered, a risk assessment will be conducted. Prior to conducting the risk assessment, the participant will be advised that if there is a concern of risk of harm to themselves or others, concerns will need to be passed on to another party, such as their GP or clinical care team.

#### Duty of care

We will use YTU standard operating procedures to support researchers to report to GPs or responsible services instances where there are concerns about the health of the participant. Normal NHS indemnity procedures will apply as participants are recruited from NHS sites. The Sponsor (UoY) will also provide standard public liability insurance to meet the potential legal liability of the sponsor for harm to participants arising from the design and management of the research.

#### Researcher safety and lone working

We will use the YTU standard operating procedures/UoY Department of Health Sciences policy for fieldwork and lone working. All researchers tasked with fieldwork will undertake lone worker training and conduct a risk assessment with their line manager about the specific tasks to be carried out.

#### Participant withdrawals

Participants will be able to withdraw from the trial at any point without having to provide a reason and without it affecting their usual care or any benefits to which they are entitled. If a participant decides to withdraw, their quality of care will not be compromised.

The participant’s clinical team will also be able to withdraw participants if they lose capacity or become unfit to continue.

There are three categories of withdrawal: withdrawal from follow-ups, withdrawal from intervention (ie, withdrawal from engaging with Coaches and workbook) or full withdrawal. Where withdrawal is from intervention only, follow-up data will continue to be collected from the participant. Data provided by participants who decide to withdraw will be retained for analysis up until the point of withdrawal.

### Trial oversight

A Trial Management Group will monitor the day-to-day management of the trial. An independent PSC will have oversight of the trial and, due to the low-risk nature of this trial, it will also undertake the role of the Data Monitoring Committee.

